### Screening and assessments

#### Screening

Participants will be screened for eligibility over the phone using the FRAIL Screen [22] and demographic- and health-related information will be collected. Medical clearance and serum creatinine investigation will then be obtained from the participants’ general practitioner before a home visit is scheduled for further screening. The home visit will include the Rapid Cognitive Screen (RCS) [25], the Charlson Co-morbidity Index [29], the Geriatric Depression Screen-5 (GDS-5) [30], Katz Activities of Daily Living (KATZ ADL) [31] and a safety check to ensure that participants exercise in a safe home environment. The screening process over the phone will take approximately 5 min and the home assessments will take approximately 30 min for each participant. The Short-Form Health Survey-36 (SF-36) [32] and the Lawton Instrumental Activities of Daily Living (Lawton iADL) [33, 34] questionnaire will be completed by the participants as self-assessments. At the completion of the screening, inclusion and exclusion criteria will be reviewed by the research team’s coordinator, and participants who fulfil all eligibility criteria will be enrolled into the 6-month nutrition and exercise intervention.

#### Completion of baseline, 3- and 6-month assessments

At baseline and at 3 and 6 months after commencing the nutrition and exercise intervention, assessments will be performed at the participants’ closest study centre (currently two locations including the Queen Elizabeth Hospital in the western suburbs and the Centre for Physical Activity in Ageing in the north-east of the city).

Baseline assessments will be conducted approximately 1 week after participants have completed the screening process and been enrolled into the study. These assessments will take approximately 1 h per participant and include the Trail Making Test [35], gait speed, grip strength (using a handgrip dynamometer) [36], Short Physical Performance Battery (SPPB) [37], Timed Up and Go Test (TUG) [38], bioelectrical impedance analyses (BIA) [39], 24 h dietary recall [40] and an accelerometer attached to the participant’s thigh [41]. The accelerometer will be collected 1 week later. At that time, participants will commence their exercise program (with the first session being a centre-based exercise class), consuming their allocated twice daily protein supplements.

The RCS [25], the Charlson Co-morbidity Index [29] and the Self Mini Nutritional Assessment (MNA-SF) [42, 43] will be conducted only at baseline to determine the participants’ risk of cognitive impairment, 5-year mortality and malnutrition.

A timeline of the screening process, interventions and assessments is displayed in Table 1. An overview of the assessment tools used to measure the potential primary and secondary outcomes related to the patient-centred objectives for the main trial at baseline and at 3 and 6 months is displayed in Table 2.

**Table 1 Tab1:**
[figure not shown]
Schedule of enrolment, interventions and assessments

**Table 2 Tab2:** EXPRESS Study assessments and cutoff criteria

EXPRESS Study assessments	Cut-off criteria		
Demographic information			
Charslon Comorbity Index	≤3 low risk	4–5 moderate risk	≥6 high risk
Rapid Cognitive Screen	8–10 normal	6–7 mild impaired	5 dementia
Mini Nutritional Assessment-Short Form	12–14 normal	8–11 at-risk	0–7 malnourished
FRAIL Screen	0 robust	1–2 pre-frail	≥3 frail
Katz Activitis of Daily Living	6 full function	4 moderately impaired	≤2 severely impaired
Lawton Instrumental Activities of Daily Living	0–3 high depended	4–6 moderate dependent	7–8 independent
Short-Form Health Survey-36			
Geriatric Depression Scale-5	≥2 answers: depression		
Trail Making Test	Part A: >78 s deficient	Part B: >273 s deficient	
Nutritional recall			
Gait speed	♂ 0.65/0.76 m/s (≤173/>173 cm)	♀ 0.65/0.76 m/s (≤159/>159 cm)	
Grip strength	♂ 29–32 kg according to BMI	♀17–21 kg according to BMI	
Short Performance Physical Battery	Limitation: 0–3 severe, 4–6 moderate, 7–9 mild, 10–12 minimal		
Timed Up and Go	<12 s normal mobility	≥12 s limited mobility	
Bioelectrical impedance analyses			
Accelerometer	Low activity ♂ <383 kcal/week	Low activity ♀ <270 kcal/week	

♂ male ♀ female

### Compliance and safety

Compliance diaries will be handed out to participants with instructions provided on how to complete them; specifically, they will be asked to record the timing and number of supplements consumed per day. The researchers will check compliance with the supplements and exercise prescription on a weekly basis for the first 2 weeks and then every 2 weeks thereafter if no problems are evident. If the study team identify that a participant’s compliance to the planned number of exercise sessions per fortnight, or the planned number of protein sachets, is less than 70% (i.e. <7 exercise sessions attended or <20 sachets consumed), the research exercise physiologist and dietitian will respectively interview the participant to assess any difficulties and identify strategies that could facilitate compliance.

For participants who have glomerular filtration rates (GFR) of >30 but ≤60 ml/min/1.73 m^2^, the GFR will be retested at 3 and 6 months, and if deterioration is noted (very unlikely), the medical registrar will liaise with the general practitioner and the participant for further assessment and management. Protein supplementation can be safely prescribed up to 1.2 g/kg body weight/day where GFR is >60 [27].

Adverse events (AEs), that is, any untoward medical occurrences (i.e. pain, discomfort, wind, headaches, noticeable difference in body and memory) will be investigated during all visits, whether or not they are related to the study product or physical regimen. The events will be reviewed by the study’s medical registrar and participants will be referred to the research physician as required.

### Statistical analyses

Statistical advice has been provided by a co-investigator (KL) who is a professional biostatistician; she will be responsible for overseeing all statistical analysis for the team. Descriptive analyses will be used to assess the completeness and variability of the outcomes using means, medians, standard deviations and ranges as appropriate. Mean and median outcomes within each group will be presented with 95% confidence intervals to help inform power calculations for a possible definitive trial. A preliminary assessment of the efficacy of the treatment will also be conducted via an intention-to-treat analysis. For each study outcome, the change from baseline after 3 and 6 months will be compared between the two study arms. These analyses will be estimated in an ANCOVA model with the 3- and 6-month value as outcome, and the baseline value age, gender and frailty status as covariates. The resulting treatment effect will be reported as the least square mean and 95% confidence interval for the primary outcomes of gait speed, grip strength and physical performance. A plot of changes over time for pre-frail and frail participants will be used to observe whether changes in the frailty status can be seen.

If recruitment is going to take substantially longer than 12 months, an interim analysis will be performed on the numbers of participants who have completed the study within that period, and a decision will be made as to whether the study is feasible to complete within a reasonable timeframe of an additional 12 months.

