### Study design

A randomised, parallel, control pilot study will be conducted in a community setting. Participants will be assessed at baseline and at 3 and at 6 months. Participants will be able to withdraw from the study at any time and will have their final assessments completed within 1 week of withdrawal.

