### Participants

Participants will be eligible for this study if they are aged 65 years and older, able to converse in English, live in the community and are identified as being pre-frail (i.e. have a score ≥1 but <3 out of 5) or frail (i.e. have a score ≥3 out of 5) using the FRAIL Screen [22], including the following five questions:Are you fatigued?Do you have difficulties walking up one flight of steps?Are you unable to walk at least one block?Do you have more than five illnesses?Have you lost more than 5% of your weight in the past 6 months?

Participants with dementia (i.e. score 5 or less out of 10) as per the Rapid Cognitive Screen [25], severe renal impairment (eGFR ≤30 mmol/L) and those unable to comply with the exercise or nutrition study protocol will be excluded.

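### The 6-month ANCOVA makes no use of the 3-month values of participants lost afterwards; a repeated-measures model on the same data would, and would settle whether one model or two is meant

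*Protocol article*

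**What the plan says.** Everyone is measured three times: "Participants will be assessed at baseline and at 3 and at 6 months" (Study design).

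The efficacy analysis is in Statistical analyses:

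- Purpose: "A preliminary assessment of the efficacy of the treatment will also be conducted via an intention-to-treat analysis".
- Contrast: "For each study outcome, the change from baseline after 3 and 6 months will be compared between the two study arms".
- Model: "These analyses will be estimated in an ANCOVA model with the 3- and 6-month value as outcome", with "the baseline value age, gender and frailty status as covariates".
- Reporting: the treatment effect, in the singular and without a named visit, as the "least square mean and 95% confidence interval for the primary outcomes of gait speed, grip strength and physical performance".

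No visit term, arm-by-visit term or within-person covariance is named. People who withdraw "will have their final assessments completed within 1 week of withdrawal" (Study design), but the article does not say how that measurement enters the 3- or 6-month comparison. It gives no sample size, expected drop-out rate, SD or between-visit correlation.

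**The concern.** Two follow-up values per person are assigned to one named model, and the wording allows two constructions.

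1. **One ANCOVA per visit.** Each model uses whoever has that visit's value. The 3-month model keeps people who leave later, but the 6-month model learns nothing from their 3-month results.
2. **One ordinary ANCOVA holding both visits.** Two correlated values from the same person are then counted as independent, and the confidence interval is too narrow.

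The first matters here because retention is part of the primary aim, and the Discussion says that earlier trials in frail older people ended with few completers. The stake is the effect estimate and interval for gait speed, grip strength and physical performance. Efficacy is preliminary, but under Feasibility objectives the pilot is meant to inform the size and potential efficacy of the main trial.

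**Working it through.** The plan has no figure of its own to reproduce. All values below for sample size N, drop-out proportion d and correlation ρ are assumptions; ρ is the correlation between the 3- and 6-month values given baseline.

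**Step 1. One ANCOVA per visit, random drop-out after month 3.** For the 6-month arm effect,

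variance(repeated measures) / variance(6-month ANCOVA) = 1 − ρ²d.

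| d | ρ = 0.5 | ρ = 0.7 | ρ = 0.8 |
|---|---|---|---|
| 10% | 0.975 | 0.951 | 0.936 |
| 20% | 0.950 | 0.902 | 0.872 |
| 30% | 0.925 | 0.853 | 0.808 |

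At d = 20%, ρ = 0.7: 1 − 0.49 × 0.20 = 0.902. The interval is then √0.902 = 0.95 times as wide. With d = 0 the ratio is 1, so the whole gain comes from people lost after month 3.

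Simulation check (3,000 trials, no true effect, baseline correlation 0.6, ρ = 0.7, d = 20%): variance 0.0508 against 0.0573 at N = 60 (ratio 0.89), and 0.0253 against 0.0283 at N = 120 (ratio 0.89). The 6-month ANCOVA had type I error 0.054 and 0.053, so it is valid under random drop-out.

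**Step 2. One ANCOVA per visit, drop-out that depends on the 3-month value.** With monotone drop-out the two 6-month estimates differ by

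b × (3-month arm contrast among those still present at 6 months − 3-month arm contrast among all),

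where b is the slope of the 6-month value on the 3-month value given arm and baseline. If drop-out works the same way in both arms, the bracket is near zero. It opens only when the mechanism differs by arm.

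- *Scenario A* (N = 60, baseline correlation 0.7, base drop-out 25%, drop-out tied to the 3-month residual in one arm only, true effect 0.5 SD, 3,000 trials): ANCOVA bias 0.145 SD at ρ = 0.6 and 0.195 SD at ρ = 0.8; repeated-measures bias 0.000 and −0.001. The two results agree with the formula, since 0.145/0.6 and 0.195/0.8 are both 0.24.
- *Scenario A with the same mechanism in both arms*: bias near zero for both methods; the ANCOVA variance is 1.05 to 1.09 times the repeated-measures variance.
- *Scenario B* (no true effect, drop-out driven by the 3-month value in opposite directions in the two arms, about 20% lost, ρ = 0.7, 3,000 trials): ANCOVA bias 0.196 SD (N = 60) and 0.190 SD (N = 120), type I error 0.13 and 0.22; repeated-measures bias 0.002 and −0.004 SD.

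**Step 3. Both visits as independent rows.** The true variance of the arm effect is (1 + ρ) times the variance the model reports, so

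coverage of a nominal 95% interval = 2Φ(1.96/√(1 + ρ)) − 1.

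| ρ | 0.3 | 0.5 | 0.7 | 0.8 |
|---|---|---|---|---|
| coverage | 91.4% | 89.1% | 86.7% | 85.6% |

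Simulated type I error at ρ = 0.7 with 20% random drop-out was 0.143 (N = 60) and 0.135 (N = 120), against 1 − 0.867 = 0.133 from the formula. These figures hold only if the second construction is what is meant.

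**The case against.** Comparing change after 3 and 6 months by ANCOVA is most naturally one model per visit, a standard and valid method. That stands. Several stronger readings that a reader might infer are therefore not supported:

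- **That visits are treated as independent.** The article never says so. The coverage figures in Step 3 show why the wording should be settled; they do not describe the plan.
- **That this is a completer analysis.** Per-visit ANCOVA is available-case. The 3-month model keeps later drop-outs, and the withdrawal assessment may supply some values. If it stood in for a missed visit, the gain in Step 1 would shrink.
- **That it breaks intention-to-treat.** That principle concerns analysis by randomised arm, and nothing departs from it. Rules for missing values are commonly left to an analysis plan, which is not shown here.
- **That drop-out linked to 3-month progress is enough to cause bias.** It must act differently by arm. Both arms do the same exercise and take closely matched, blinded supplements, so this cannot be presumed.
- **That ANCOVA is an error for frailty status.** Frailty status does fall under each study outcome, but least square means are promised only for the three primary outcomes. If the frailty class is the outcome, entering it twice is redundant and leaves the arm effect unchanged. In 400 simulated trials, ANCOVA on three levels against a proportional-odds model gave type I error 0.045 against 0.045 (N = 60) and 0.050 against 0.045 (N = 120), and power 0.34 against 0.35 and 0.565 against 0.57.

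It is also fair that efficacy is secondary, and that the article ties the main trial's power calculation to within-group means and medians rather than to this contrast. That limits the consequence. It does not remove the ambiguity or the unused 3-month information.

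**Conclusion.** The point holds as a cheap improvement. The model sentence leaves open whether one model or two is meant. On its natural reading the analysis is valid under random drop-out but sets aside information that the trial will have collected, in a population where losses are expected.

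Under random drop-out the gain is modest: about 5 to 10% lower variance at 20% loss and ρ of 0.5 to 0.7, or an interval roughly 2.5 to 5% narrower (√0.95 = 0.975, √0.902 = 0.950). The protection against bias is larger, up to about 0.15 to 0.20 SD in the scenarios tried, but it depends on drop-out following the 3-month result differently in the two arms. All of these sizes rest on assumed N, ρ and d.

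**What to change.** For gait speed, grip strength and physical performance, replace the model sentence with a repeated-measures mixed model:

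- outcomes: the 3- and 6-month values;
- fixed effects: arm, visit, arm-by-visit, baseline value, baseline-by-visit, and the covariates already named (age, gender, frailty status);
- unstructured within-person covariance, with Kenward-Roger degrees of freedom because the pilot may be small;
- main estimate: the 6-month difference in least square means between arms with its 95% CI, the 3-month difference being reported beside it.

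The cost is a change of wording and a little more analysis work, with no new data or visits. The model assumes that data are missing at random given the observed values, and the report should say so. An ordinal model for frailty status, with the baseline FRAIL score entered once, is optional. It would make the result easier to interpret, but it assumes proportional odds and may meet sparse cells in a small pilot.

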## Discussion

Frailty is a major public health issue. It directly, and also indirectly through increased disability, contributes to increased health and aged care costs of elderly populations around the world [2]. Frailty is a continuum of accumulated lifetime assaults on the body that compromises physical and/or mental equilibrium, predisposing older adults to increased dependency on healthcare resources [4]. Adults who are identified as being pre-frail have an increased risk over the next 3 to 4 years of becoming frail, requiring greater support in performing activities of daily living and maintaining independence [7]. This means the early detection of frailty is pivotal for timely interventions that may assist in managing this geriatric condition and reducing healthcare costs, and to date, there remains a paucity of information about lifestyle interventions that may be beneficial for this target population.

While exercise in combination with protein supplementation has been shown to positively impact a variety of physical and/or psychological health attributes in pre-frail and/or frail older people, several aspects related to the study design of previous research still limit the interpretation of the collective results. Accordingly, the proposed study protocol hopes to extend the current knowledge in this area by specifically examining the feasibility, tolerability, efficacy and safety of consuming twice daily protein supplements in the context of a multicomponent exercise program.

Recruiting and retaining frail older adults into community-based intervention programs is a major issue that prior research has identified and is generally the reason why many studies report relatively small numbers of participants (and especially small numbers of completers) [44]. Accordingly, this study has been designed to represent and test the efficacy of a pragmatic, community-led, exercise and nutrition program which is based on postulated hypotheses that remain to be debated within the fields of nutrition and gerontology [27]. Addressing many of the methodological limitations noted in the background literature, this study protocol should optimise the ability to recruit pre-frail and frail older participants who want to remain independent and engaged within their communities. For example, participants will be diagnosed as being pre-frail or frail using the FRAIL Screen which can be easily used in all primary care settings because it is simple and quick; as such, a variety of recruitment channels will target to promote the study including general practice clinics, age-care organisations, groups that are dedicated to supporting older adults and also the general public via social media channels. Secondly, on a weekly basis throughout the 6-month intervention, our multi-disciplinary research team consisting of geriatricians, age-care nurses, exercise physiologists and dietitians/nutritionists will be supporting each participant—albeit in a group setting—to build a study community that should assist with maintaining participant motivation. Thirdly, the personalised tailoring of the exercise program should also maximise the likelihood that each participant will progressively improve their strength, flexibility, balance and endurance, and thereby improve their physical health and overall wellbeing.

Regarding the protein supplementation part of the program, participants will be instructed to consume the daily protein supplements in close proximity (i.e. <1 h) to the completion of the exercise and in between meals on non-exercise days. The timing of consumption was based on the ongoing theory that resistance training increases amino acid delivery to the muscles, as well as absorption; hence, participants should be consuming an adequate amount of substrate, in a timeframe, that should maximise stimulation of muscle protein synthesis [45]. Moreover, there is consistent evidence that whey protein rather than casein, milk, soy or pea is more superior at promoting muscle protein synthesis or building muscle mass due to its higher quality (i.e. higher free amino acid to total amino acid content and especially its high essential branched-chain and leucine content) [46]. However, other plant-based proteins such as rice or pea protein are popular with consumers and while they are of lower protein quality, evidence regarding their impact on muscle mass, strength or physical performance/function, particularly when consumed over several months, remains scant. Therefore, this study will directly compare a whey protein supplement (i.e. higher quality protein) to a rice protein supplement (i.e. a lower quality protein) to address this concern. Long-term tolerability and safety to both proteins, as well as to the exercise program, will also be an important issue addressed within this study.

## Conclusion

This study is expected to provide much needed insight into the feasibility of recruiting and retaining frail older adults into community-based intervention programs, while providing knowledge relating to the safety, tolerability and benefits of a combined exercise and protein supplement program designed to halt or reverse the transition of physical frailty in the community. If shown to be effective, this strategy could be used to inform the design of cost-effectiveness trials which will be necessary if public health policy makers and funders are to be strategically influenced. Evaluation of the collective findings from current and future research will be critical to refine and extend the current best practice clinical guidelines for community-dwelling older people who are pre-frail or frail.

## Abbreviations

AE: Adverse event
BIA: Bioelectrical impedance analyses
CT: Computer tomography
GDS-5: Geriatric Depression Screen-5
GFR: Glomerular filtration rates
KATZ ADL: Katz Activities of Daily Living
Lawton iADL: Lawton Instrumental Activities of Daily Living
MNA-SF: Self Mini Nutritional Assessment
RCS: Rapid Cognitive Screen
RPE: Rating of perceived exertion
SF-36: Short Form Health Survey-36
SPPB: Short Physical Performance Battery
TUG: Timed Up and Go Test
